#### Data collection and analysis

Echo scans and clinical and demographic data will be collected.

Demographic data, including birth gestation in weeks, birth weight, sex, Apgars, chorioamnionitis, maternal hypertension, antenatal steroids, and magnesium sulphate, will be collected.

Functional neonatal echo scans will be performed, collected and stored on the 5th and 9th DABs of the recruited preterm infants. They will be collected as per the developed echo image acquisition guide, which is in compliance with the expert consensus statement produced by the American Society of Echocardiography in collaboration with the European Association of Echocardiography and the Association for European Pediatric Cardiologists [21]. Numerous echo parameters, such as global and segmental strain and strain rate for right and left ventricles (RV and LV), tissue Doppler imaging (TDI) of RV free wall, septal and LV lateral wall to measure the S, E’ and A’ waves together with isovolumic contraction and relaxation times, will be collected. Other echo parameters related to pulmonary arterial pressure, cardiac function and ductus arteriosus (DA) assessments such as tricuspid regurgitant jet, pulmonic valve insufficiency, pulmonary artery acceleration time (PAAT), right ventricle ejection time, tricuspid annular plane systolic excursion (TAPSE), mitral annular plane systolic excursion (MAPSE), shortening fraction of the LV and DA size and shunt assessment, will be collected too. Also, right ventricular systolic pressure and myocardial performance indices of RV and LV, will be calculated.

These scans will be analysed using a specialised cardiology analytic system (TomTec, Germany).

In addition, clinical data, vital signs, current weight and ventilatory support will be collected.

The distribution of all continuous variables will be visualised to check for normality and summarised using appropriate descriptive statistics. Preterm infants will be categorised into two groups: (i) moderate or severe BPD and (ii) mild or no BPD.

Velocities and displacements are dependent on cardiac size. Therefore, it is crucial to normalise the measurements taken for cardiac size [22]. The left ventricle septal length will be used to normalise all echo measurements of interest.

The collected echo parameters measurements, clinical data, vital signs, current weight and ventilatory support will be analysed and compared between the cases and controls. Also, if any, missing data will be quantified so appropriate modifications will be implemented to improve the data collection process in a definitive large study.

The comparison between the two groups will be further assessed using the t-tests conducted for normally distributed continuous variables and Mann–Whitney *U* tests for non-normally distributed variables. Chi-squared tests will be conducted to compare categorical variables between groups. The generated descriptive statistical data will inform the sample size estimation for the definitive large study. Also, establishing the most sensitive echo parameters in recognising RV dysfunction will facilitate the construction of the BPD prediction model.

The prediction model will mainly be consisted of the most sensitive echo parameter(s) with incorporation of the gestational age in weeks at birth, oxygen requirements and ventilatory support at the time of the echo scans.

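### Septal-length normalisation is justified only for velocities and displacements but is prescribed for every echo measurement, including strain, time intervals, ratios and pressure

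*Protocol article*

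**What the plan says.** The protocol article deals with normalisation in three consecutive sentences under WP-1, Data collection and analysis. The reason comes first: "Velocities and displacements are dependent on cardiac size". The text then concludes that adjustment for cardiac size is essential, citing a reference. The rule follows: "The left ventricle septal length will be used to normalise all echo measurements of interest". No exception is stated.

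Earlier in the same section is the list of measurements. Some fit the stated reason: the tissue Doppler S, E' and A' waves (velocities), and TAPSE and MAPSE (displacements). Many do not:

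- strain and strain rate of both ventricles, which are already expressed relative to length;
- time intervals: "isovolumic contraction and relaxation times", and "pulmonary artery acceleration time (PAAT), right ventricle ejection time";
- a ratio: "shortening fraction of the LV";
- a pressure and two indices: "right ventricular systolic pressure and myocardial performance indices of RV and LV".

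The section then splits infants into moderate-or-severe BPD and the remainder. It compares the echo parameters between these groups by t-test or Mann–Whitney test, with no adjustment mentioned. The resulting descriptive data are to inform the sample size of the definitive study. The most sensitive parameter or parameters go into a prediction model that also contains gestational age, oxygen requirement and ventilatory support.

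**The concern.** The rule is wider than its own justification. Dividing a displacement by a heart length removes the part that merely reflects heart size. Dividing a time, a ratio or a percentage strain by the same length does the opposite: it puts the reciprocal of heart size into a quantity that did not contain it.

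If the two groups differ in heart size, such a parameter will differ between them even when it has no relation to BPD. The same mechanism can hide a real difference when the abnormal direction is downwards, as with a reduced strain magnitude or shortening fraction, because a smaller divisor pushes the value back up.

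This matters because identifying the most sensitive parameter is a secondary outcome, building a model on a sensitive parameter is described as a key progression criterion, and the group summaries feed the next study's sample size. A SAP that followed this sentence would inherit the problem.

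**Working it through.** The plan has no figure to reproduce: the target of 40 is pragmatic, with no alpha, power, effect size or SD. The check therefore asks what the rule does to a parameter that is independent of heart size.

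**Inputs from the document**
- 40 infants; one third of eligible infants developing moderate-to-severe BPD (Recruitment and sample size): 40/3 = 13.3, so 13 against 27.
- Unadjusted two-group comparison (WP-1, Data collection and analysis).

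**Assumptions not in the document**
- Normalise means divide by septal length.
- Mean septal length is a fraction d shorter in the BPD group, with d = 5%, 10% or 15%.
- Septal-length CV 8%; parameter CV 10% to 30%; two-sided alpha 0.05.

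**Size of the artefact.** For a parameter with the same mean in both groups, the ratio of normalised means is 1/(1 − d):
- d = 5%: 1/0.95 = 1.053, an apparent excess of 5.3%
- d = 10%: 1/0.90 = 1.111, an excess of 11.1%
- d = 15%: 1/0.85 = 1.176, an excess of 17.6%

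**False-positive rate.** Simulation, 20,000 datasets per cell, t-test on parameter/septal length, no true difference:

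| Parameter CV | d = 0 | d = 5% | d = 10% | d = 15% |
|---|---|---|---|---|
| 10% | 5.1% | 21.5% | 66.6% | 95.7% |
| 15% | 5.1% | 14.5% | 43.9% | 79.5% |
| 20% | 4.9% | 10.8% | 30.2% | 59.8% |
| 30% | 4.9% | 8.0% | 18.3% | 34.6% |

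Raw values gave 4.8% to 5.1% in every cell. Holding the septal-length SD, rather than its CV, equal in the two groups gives 11.3%, 30.8% and 60.3% in the 20% row, so that choice hardly matters.

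**Masking.** With a true reduction t, the ratio of normalised means is (1 − t)/(1 − d). At parameter CV 15%:
- t = 10%, d = 10%: 0.90/0.90 = 1.00. Detection in the correct direction falls from 48.8% raw to 2.7%.
- t = 15%, d = 10%: 0.85/0.90 = 0.944. Detection falls from 82.5% to 15.8%.
- t = 5%, d = 10%: 0.95/0.90 = 1.056. The test is significant in the wrong direction 15.5% of the time.

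**Where the rule is sound.** A displacement proportional to heart length, divided by that length, has a group ratio of (1 − d)/(1 − d) = 1. The rule does what it should for the measurements its rationale covers.

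**The case against.** **Scope.** The three sentences can be read as one argument, with the final phrase pointing back to the velocities and displacements just named. The article condenses a fuller protocol, and the reference behind the rule cannot be seen here. This reading is possible, but the text does not state it, and the long parameter list earlier in the section makes the wider reading natural. If the narrow meaning was intended, the fix only writes it down.

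**Division.** The article says normalise, not divide. Division is the ordinary meaning and no other method is described, but it remains an inference.

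**Size difference.** The bias needs septal length to differ between the groups, and no figure is given. The Abstract links birth before 32 weeks to BPD, but every participant is born before 32 weeks, so that sentence shows no gradient within the cohort. A less mature, smaller BPD group is plausible but not documented. This objection stands, which is why results are shown as a range that returns to 5% when d = 0.

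**Gestational age in the model.** A reader might infer that the artefact passes straight into the prediction model. The document does not support that. When the simulation above (parameter CV 20%) was rerun with the septal-length difference arising entirely through gestation, adding gestation as a covariate brought the rejection rates to 5.3%, 5.4% and 5.5%. That is the favourable case; if heart size differs for other reasons, some bias could remain. The unadjusted comparisons and group summaries are not protected in either case.

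**Selection.** A reader might also infer that the most sensitive parameter is the one with the smallest p-value. The article does not say so; the false-positive rates describe the planned tests, not a documented selection rule.

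**Conclusion.** The point holds as a mismatch between rule and rationale: the article fixes septal-length normalisation for all measurements of interest while justifying it only for velocities and displacements. For the size-independent parameters listed, and on the two assumptions of division and a shorter septal length in the BPD group, the unadjusted comparisons are biased. The apparent excess is about 5%, 11% or 18% for septal length 5%, 10% or 15% shorter, with false-positive rates of about 11%, 31% and 60% at parameter CV 20% and septal-length CV 8%. True reductions can be hidden or reversed. The descriptive data that inform the definitive study's sample size carry the same distortion.

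The document does not establish that a spurious difference will occur, how large it would be, or that it would survive in a model containing gestational age. The scans are stored, the study is an exploratory feasibility study, and the model is to be tested later in a large multi-centre trial, so the matter can be put right at analysis. It should be fixed before analysis; it is not a fatal flaw.

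**What to change.** Replace the single normalisation sentence with a rule that sorts the parameters:

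- **Normalised by LV septal length:** measurements expected to scale with cardiac size, namely the tissue Doppler S, E' and A' velocities, TAPSE and MAPSE. State the method (for example, division).
- **Analysed raw:** strain and strain rate, isovolumic times, PAAT, RV ejection time, shortening fraction, myocardial performance indices and RV systolic pressure.
- **Decided explicitly:** TR jet velocity, because the stated rationale refers to velocities without qualification, and ductus arteriosus size, which is a linear dimension. The article should say how each is treated and why.
- **Reporting:** give raw values beside normalised ones, and summarise septal length by BPD group so that readers can see whether the divisor differs.

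The cost is a few lines in the analysis section, written before the group comparison is run. It needs no new scans, no new data and no change to recruitment.

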### WP-II

This WP will examine the parental notes written in their preterm infants’ NICU diary. The parental diary in the intensive care setting is used to help parents cope with the situation by writing down their feelings [23, 24]. There is a paucity of research project regarding the use of parental perceptions recorded in the NICU diary about their children’s health. Therefore, the diary recordings of the participating preterm infants’ parents about the respiratory function changes observed by the parents in the first 10 DABs will help in understanding the significance of parental perception of the progression of their infants regarding the respiratory function. Mining and examining these data will highlight the strength of the correlation between the parental observations of their children’s health in the first 10 DABs in recognising early BPD symptoms.

#### Objectives

To understand parental perceptions regarding their preterm infants’ health progression in the first 10 days of postnatal life and its correlation with the echo scans findings.

#### Study design and settings

This is an embedded qualitative study that explores the parental perception of their infants’ health written in a diary.

This study will be conducted in the regional tertiary NICU, UHP, Plymouth.

#### Recruitment

Screening and consenting will be the same as those described in WP-I. The research team aims to obtain copies of the NICU diaries from all parents whose preterm infants participated in WPI (40 diaries or the number achieved within the recruitment period of 1 year).

##### Inclusion criteria

Parents of preterm infants recruited in the REPORT-BPD feasibility studyEnglish speaking

##### Exclusion criteria

Non-English speaking

#### Data collection and analysis

Once consent is obtained from the parents on the second DAB of their infants, the research team will give the parents a NICU diary along with a study leaflet about ‘how to write a NICU diary’. The diary comprises a small notebook consists of 50 blank pages. A NICU diary writing guide will be given to parents advising what they might write in NICU diary such as reflections, feelings, comments about their child health and progress. There are no limitations on the frequency of notetaking by parents, i.e. they can choose to write as little or as much as possible. On the 10th DAB, the research team will obtain a copy of the parental notes documented in their preterm infants’ NICU diary from the 2nd to 10th DAB, as the original copy is for their keepsake. Therefore, only the records of the NICU diary within the first 10 DABs will be collected. The parental notes written in the NICU diary will be transcribed for analysis.

The transcripts will be imported into the qualitative analysis software programme NVivo to enable the organisation and analysis of textual data. A thematic analysis will be deployed and comprise the following six steps [25]. The first step will involve familiarisation with the text, where two researchers ([name] (WM) and [name] (JL)) will independently read the transcripts. In the next step, these researchers will independently code the text by allocating text fragments to codes. The codes might be revised during the process of reading the transcripts. In step three, the two researchers will discuss the results of individual codes (sub-themes) and refocus their analysis on identifying potential themes. Step four will involve two levels: level 1 will involve scrutinising the identified themes to generate an accurate thematic map, and in level 2, the researchers will examine whether the generated thematic map accurately reflects the codes extracted from the datasets. The fifth step will involve defining and naming the themes by further refining them. Finally, the sixth step will involve creating the final report, which will be focused on writing a concise, coherent, logical, non-repetitive and interesting account of the data story [25].

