1. Born at < 32 weeks gestational age. 2. The echo scans are indicated as per the recommended neonatal practice [19]: i. Preterm infants who require mechanical ventilation or non-invasive respiratory support (CPAP ≥ 4 cm H_2_O, high flow ≥ 4 L/min) ii. Detection of a cardiac murmur in the first 3 days after birth iii. Assessment of patent ductus arteriosus (PDA) iv. Preterm infants have central line in-situ, so echo is needed to assess line position	1. Preterm infants with major congenital anomalies, such as pulmonary hypoplasia or congenital heart disease (except PFO or PDA) 2. Preterm infants with a poor prospect of survival 3. Preterm infants whose parents do not consent 4. Preterm infants who are still in need of blood pressure supporting medications, such as, (inotropes) when the study echo scans are due 5. Preterm infants need inhaled nitric oxide gas when the study echo scans are due

*PDA* patent ductus arteriosus, *PFO* patent foramen ovale

All parents will be spoken to in person by the neonatal research team, who are also part of the neonatal clinical team in the antenatal wards in the delivery suite antenatally or in the neonatal unit postnatally. A clear verbal explanation will be provided about the trial and why the parents and their preterm infants are invited to participate. They will also be given a participant information sheet (PIS) and an informed consent form (ICF). If the parents wish for their preterm infant to be recruited for the study when feel well-informed and satisfied with the explanations provided, they will be asked to sign the ICF.

Consent will be sought for WP-I and WP-II from the parents of the eligible-for-inclusion preterm infants on the second DAB. All participants will be informed that they are free to withdraw from the study at any time without giving reasons and without prejudicing further treatment.

A delegation log will be maintained to ensure that the medical practitioners registered as study delegates participating in the consenting process of this study are duly authorised, have completed the Good Clinical Practice (GCP) training, are experienced clinicians and competent to participate according to the ethically approved protocol, principles of GCP and Declaration of Helsinki [20].

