**Work package—I**	• Establishing sensitive and feasible echo parameters for detecting right ventricle dysfunction associated with early BPD pulmonary vascular changes • Suitability of eligibility criteria and sample characteristics • Fidelity to the study procedures such as recruitment, data collection including echo scan performance at the set time points • Recruitment, accrual, and retention rates
**Work package—II**	• To gain an understanding of how strong the correlation between the parents’ views of their infant’s health development during the first 10 days of postnatal life and the findings of echo scans at the same period
**Work package—III**	• To gain an understanding of parents and healthcare professionals in participating in the study and identify barriers and enabling factors to inform the methods a full trial

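### WP-II relates the whole day 2–10 diary to echo scans done on days 5 and 9, so some agreement could reflect scan information passed on to parents; dating and tagging entries would let this be checked (minor)

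*Protocol article*

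**What the plan says.** All references are to the protocol article.

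- **Diary window.** WP-II, Data collection and analysis, says when the diary is handed over: "Once consent is obtained from the parents on the second DAB of their infants, the research team will give the parents a NICU diary". On day 10 the team copies the parents' notes in the "NICU diary from the 2nd to 10th DAB, as the original copy is for their keepsake". The section adds that "only the records of the NICU diary within the first 10 DABs will be collected". On how often parents write: "There are no limitations on the frequency of notetaking by parents". The writing guide is described as suggesting reflections, feelings and comments on the child's health and progress. The article does not mention dating of entries.
- **What the diary is compared with.** The WP-II objective is to understand parental perceptions and how they correlate with the echo findings. Table 3 makes the strength of that correlation the WP-II outcome measure, with parents' views taken "during the first 10 days of postnatal life and the findings of echo scans at the same period". The WP-II introduction gives the purpose: the value of parental observations "in the first 10 DABs in recognising early BPD symptoms".
- **When and why the scans are done.** WP-I, Data collection and analysis, puts them on days 5 and 9. Table 2 makes clinical indication an inclusion criterion: "The echo scans are indicated as per the recommended neonatal practice". The text after Table 2 says that parents are approached by "the neonatal research team, who are also part of the neonatal clinical team".
- **What is measured.** WP-I lists strain, tissue Doppler and other functional measures, together with size and shunt of the ductus arteriosus. The scans are analysed in a specialised cardiology system. Nothing is said about whether or when any finding reaches the parents.

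**The concern.** WP-II wants to learn whether parents notice something about their infant that goes with the echo picture of early BPD. For that reading, the diary text should not itself be informed by the echo. Both scans take place while the diary is being kept, and the comparison is defined over the whole period with no separation of text written before and after a scan.

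A parent who has been told something about a scan may well write it down, since the guide invites comments on health and progress. Such an entry would agree with the echo without the parent having observed anything. The comparison as stated could not tell the two sources apart. This is a different question from how diary text is turned into something that can be correlated: it would remain even with a sound score for each diary.

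**Working it through.** The plan gives no figure to reproduce here, and no sample size or power calculation bears on the point. The check is a count of calendar days, followed by a reading of the relevant sections together.

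**Inputs.** The diary runs from day 2 to day 10 (WP-II, Data collection and analysis). The scans are on days 5 and 9 (WP-I, Data collection and analysis).

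**Diary days.** 10 − 2 + 1 = 9.

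**Diary days relative to each scan.**

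| Scan | Before scan day | On scan day | After scan day | On or after |
|---|---|---|---|---|
| Day 5 | days 2–4: 3/9 = 33% | 1 | days 6–10: 5/9 = 56% | 6/9 = 67% |
| Day 9 | days 2–8: 7/9 = 78% | 1 | day 10: 1/9 = 11% | 2/9 = 22% |

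A majority of diary days therefore follows the day-5 scan but not the day-9 scan. Of the seven days before the day-9 scan, three (days 6–8) already lie after the day-5 scan.

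**Sensitivity to the first day of writing.** If parents begin on day 3, the share after day 5 is 5/8 = 63%; if on day 4, it is 5/7 = 71%.

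**Limit of the count.** These are days, not entries or words. Writing frequency is free, so the share of diary text written after a scan is unknown.

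**Could scan information reach the diary?** Three links are needed.

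1. *A scan that clinical staff would use.* Supported: Table 2 requires a clinical indication, with PDA assessment and central line position among those listed.
2. *Staff who both know the result and talk to parents.* Plausible: the research team is part of the clinical team.
3. *Parents being told a finding that is among those compared.* Not stated. Duct size and shunt are among the collected parameters and PDA assessment is a listed indication, so overlap is plausible there. For strain and tissue Doppler measures from the analysis system, the article gives no timing and no feedback route, so it is less plausible that parents hear of them by day 10.

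**The case against.** The strongest reply is that the mechanism is assumed. No section says that parents are told scan results, and time order alone does not make two measurements dependent. This stands, so the point is conditional.

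Second, what parents are likely to hear (the duct, the line) is mostly not the right-ventricular function that the study is about. This narrows the route. It does not close it, because duct findings are also collected and Table 3 speaks of echo findings in general.

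Third, a single copy on day 10 describes collection. It does not say that entries are pooled regardless of date, and the leaflet and writing guide, which are not shown in full, may ask for dates. This is fair. Dates alone would not settle the matter, though, because Table 3 defines the comparison over the whole period.

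Fourth, restricting the main comparison to entries before day 5 would work against the study's own rationale. The Discussion places the respiratory decline at day 7, and the Background has oxygen need rising at the start of the second week. Days 2–4 come before the change parents are meant to notice. Those entries would not be free of staff information either: Table 2 allows a murmur in the first 3 days or a PDA assessment as the indication, so clinical scans and conversations may come before day 5. This also stands, and the fix respects it.

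A reader might go further and infer that the comparison is circular, or that most of the diary is contaminated. The documents support neither. Circularity would need disclosure of the compared findings, and the 5-of-9 majority applies to the day-5 scan only and counts days, not text.

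**Conclusion.** The point holds as a minor one. WP-II sets out to judge the strength of a correlation between parents' views and echo findings, using diary text that partly follows the scans: 5 of 9 days after the first and 1 of 9 after the second. If parents are told any scan findings, some of the agreement could be relayed information, and the comparison as stated has no means of showing how much.

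This rests on one assumption, disclosure to parents, which the article neither states nor excludes and which is more plausible for duct findings than for measures derived in the analysis system. The size of any effect cannot be computed from the documents.

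The consequence is contained. The thematic description of the diaries is unaffected, as is the WP-I comparison of infants with and without BPD. WP-II appears in none of the progression criteria and supplies no term in the prediction model. The change is a cheap improvement and not a condition for the study to proceed.

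**What to change.** 1. In the diary writing guide, ask parents to date each entry, if it does not already do so.
2. In WP-II, Data collection and analysis, and in Table 3, add a code for statements that repeat what staff said, and repeat the diary–echo comparison without them.
3. In the same two places, add a sensitivity comparison that relates each scan only to entries written before it: the day-5 scan to entries before that scan, and the day-9 scan to entries before that one. Note when reporting the latter that some of its entries follow the day-5 scan.
4. Keep the full day 2–10 text in the thematic analysis, and do not make the entries before day 5 the main comparison.

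The cost is one line in the guide, one extra code, a sentence or two of analysis text, slightly more coding work and less text in the sensitivity comparisons. Dating has to be in place before diaries are written, since time order may not be recoverable from undated copies. The staff-information code can still be applied to diaries already collected.
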